## 11.2 Analysis of the effect variables

Five percent (5 %) will be used as significance level in all statistic tests.

The statistical analysis will look at two groups of cardiac patients separately: 1) those patients for whom all therapeutic approaches have been exhausted and 2) the rest. One joint analysis will be made if it is statistically reasonable. The statistics are compiled on an "intention to treat basis"; meaning that all enrolled patients are included in the subsequent analysis.

In the statistical analysis, subgroup analysis will be made for the patients with the highest PPS values: e.g. all patients with  $PPS \geq 75$ ; or for the highest quartile of PPS values.

"Closed test procedure" will be used to analyze data after 3 and 12 months in terms of the assessment of the treatment effect:

- First priority hypothesis: The Ull Care program improves the degree of depression measured by a MDI depression score, measured after 3 months of intervention.
- Second priority hypothesis: The Ull Care program improves health economic variables, measured after 12 months of intervention.
- Third priority hypothesis: The Ull Care program improves the frequency of clinical events, measured after 12 months of intervention.

Baseline measurements will be co-variant variables in relation to the applied stratification variable: the degree of depression measured by the MDI scale. Data from before and after the intervention will be analyzed separately. Delta values for

the active and control group respectively will be compared to analyze a possible treatment effect. All secondary and tertiary effect variables will be analyzed after the intervention through variance and regression analysis. If the premises for the proposed statistical analysis cannot be met, non-parametric analysis is used. Quality-of-life data will be analyzed to meet the directions of each of the questionnaires. All effect data will be presented a unifying table and primary, secondary and tertiary effect variables will be listed.

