## 8. Randomization procedure

The treatment is assigned randomized and with an equal number of patients in the control group and for active intervention. An independent research company electronically conducts the practical randomization ([www.larix.dk](http://www.larix.dk)).

The treatment is allocated by a minimization procedure with built-in randomness (Pocock and Simon, 1975). The minimizing will ensure an approximate balance in the number of patients in both treatment groups with respectively low and high values of the baseline parameters taken into account in the procedure. Pocock and Simon's minimization method (Pocock and Simon, 1975) will be used with a randomness parameter of 0.8. The following baseline parameters will be included:

- Age ( $< 65$ ,  $\geq 65$  years)

- Gender (male, Female)

- Heart failure (Yes, No)

- Diabetes (Yes, No)

- MDI (score  $<15$ ,  $\geq 15$ )

The result of the randomization is blinded to the investigating nurses and doctors and other who are hired to participate in the study, including the statisticians who analyze the data in relation to the main scientific article. The people conducting the training of the active group as well as patients are excluded from blinding.

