## 11. Statistics

### 11.1 Power and calculation of the size of the study population

The primary analysis is based on the depression score of the MDI questionnaire. The prevalence of depression measured as a MDI score  $\geq 20$  was found to be approximately 20 % in patients with ischemic heart disease (Olsen et al 2003; Bech P 2001). In a study with 292 office workers, the prevalence of a MDI score  $\geq 20$  was twice as high in people with a PPS measure  $\geq 60$  compared to people with PPS  $< 40$  (Ballegaard et al 2011). Against this background, it is estimated that among patients with ischemic heart disease who at the same time have an elevated PPS measure the prevalence of an MDI  $\geq 20$  is increased by 80 % compared to patients with ischemic heart disease as a whole, i.e. 36 %.

The Minimal Important Difference (MID) is set at 0.4 when the effect of active treatment is compared to control treatment. MID in terms of improvement of a MDI score is set at 5 points on the MDI scale when the active and control groups are compared. The standard deviation of improvement in both groups is set at 9 units on the MDI scale. Alfa is set at 5 %, Beta at 20 %. Against this background, 50 patients with an MDI score  $\geq 20$  are required in each group, thus 300 patients in total when safety margins of 10 % of the estimated values are included.

An interim analysis on the first 60 patients included showed, that the anticipated prevalences for MDI score were different than found. Therefore the cutpoint on the MDI scale was changed to MDI score = 15.

- Effect size is calculated from all included patients (on intention to treat basis)
- Effect size is a fraction that consists of the difference in a MDI score from before intervention till after treatment for the active group, minus the same

difference for the control group divided by the spread of the change in MDI score, when taking all patients together. In a review of all of the 12 SSRI preparations that the FDA has approved for treatment of depression, the average effect size is 0.3 (Turner et al., 2008). Example: the MDI score in active group changes from 24 to 11 ( $24-11 = 13$ ); while the MDI score for the control group changes from 24 to 14 ( $24-14 = 10$ ). This change in the MDI score is  $13-10 = 3$ ; if the spread (standard deviation) on the MDI score overall are 7.5, the effect size will be  $3/7.5 = 0,4$  ([name], 2010).

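### Section 11.2 makes separate analyses of two undefined patient groups the default and the all-patient analysis conditional, which conflicts with section 11.1 and the success criteria in section 12

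*Protocol*

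**What the plan says.** Section 11.2 opens with the error level: "Five percent (5 %) will be used as significance level in all statistic tests". It continues: "The statistical analysis will look at two groups of cardiac patients separately: 1) those patients for whom all therapeutic approaches have been exhausted"; everyone else forms the second group. Pooling is then made conditional: "One joint analysis will be made if it is statistically reasonable". The next sentence invokes intention to treat, "meaning that all enrolled patients are included in the subsequent analysis".

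Other sections point to one all-patient comparison:

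- **Section 11.1:** "Effect size is calculated from all included patients (on intention to treat basis"; the divisor is the spread of change in MDI over all patients together.
- **Section 12:** the MDI criterion requires a significant improvement of active over control and an effect size of at least 0.4, and refers to section 11.1 for the calculation. It does not mention the two groups.

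The first group appears nowhere else. It is not in the eligibility criteria (5.2 and 5.3), not among the minimisation factors that section 8 introduces with "The following baseline parameters will be included" (age, gender, heart failure, diabetes, MDI), and not among the subgroups in section 11.5. The closed test procedure in section 11.2 orders three hypotheses (MDI at 3 months, health economics and clinical events at 12 months). It does not order patient groups.

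**The concern.** Read as written, the split is the rule and the all-patient comparison is the exception. Three things follow.

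1. **The success criterion may lack its analysis.** Section 12 needs an all-patient effect size, while section 11.2 provides an all-patient analysis only if an unstated condition is met. No sentence says that the joint analysis is primary or that the split is secondary. The 12-month health-economic and event analyses depend on success being declared (sections 6.3.4 and 7), so the ambiguity carries forward.
2. **The MDI hypothesis can be tested two or three times at 5% each**, with no allocation of error between the tests.
3. **The sample size makes no allowance for separate analyses.** No group sizes are given, so power within each part is unknown.

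**Working it through.** **Inputs.** Alpha 5% for every test (11.2); "Alfa is set at 5 %, Beta at 20" % (11.1); MDI difference 5 points and SD of change 9 (11.1); effect size 0.4 (11.1 and 12); 300 patients allocated 1:1, so 150 per arm (7 and 8). The protocol does not state sidedness; two-sided testing reproduces its figure. It gives no group sizes, so the splits below are assumptions.

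**Step 1: the plan's own sample size.** n per arm = 2 × (9/5)² × (1.960 + 0.842)² = 50.9, so 51 against the stated 50. With 36% prevalence, 100/0.36 = 278; a 10% margin gives 278 × 1.1 = 306 against the stated 300. The figure reproduces, on the basis of one comparison.

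**Step 2: false positives on MDI under the null.** The two groups contain different patients, so their tests are independent.

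- Two tests: 1 − 0.95² = 9.75%.
- Two tests plus the joint test: with a fraction f of patients in the smaller group, Z(joint) = √f × Z₁ + √(1 − f) × Z₂. Simulation with 2 million replicates gives 10.9%, 11.2% and 11.5% for f = 10%, 20% and 50%.
- Pooling when a treatment-by-group interaction test has p > 0.05 (an assumed rule; the protocol gives none), otherwise testing separately: 8.7% at f = 10% falling to 8.0% at f = 50%.
- Counting only false claims of benefit: 1 − 0.975² = 4.9% for two tests, and 5.5% to 5.8% with the joint test added, against 2.5% for a single two-sided test.

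**Step 3: what section 12 does to these rates.** With 150 per arm, an all-patient effect size of 0.4 corresponds to Z = 0.4 × √(150/2) = 3.46, which under the null is exceeded about 0.03% of the time. If each part could instead use its own effect size, the chance of a false MDI success is about 1.4% for an even split and reaches at most about 2.7% for more uneven ones. The additional PPS criterion can only lower these figures.

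**Step 4: power at effect size 0.4, two-sided 5%.** By normal approximation, power = Φ(0.4 × √(n/2) − 1.96), with n per arm. The t-test values are slightly lower.

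| Analysis | n per arm | Normal | t-test |
|---|---|---|---|
| Joint | 150 | 93.4% | 93.2% |
| 20/80 split, smaller part | 30 | 34.1% | 33.2% |
| 20/80 split, larger part | 120 | 87.3% | 87.0% |
| Even split, each half | 75 | 68.8% | 68.2% |

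On the protocol's own powered subset (50 per arm, 5 points, SD 9), the joint value is Φ(2.778 − 1.960) = 79%. In each half of an even split, 25 per arm, it is Φ(1.964 − 1.960) = 50%.

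**The case against.** The strongest reply is that sections 11.1 and 12 show the intention: the effect size comes from all patients, and success also needs an effect of at least 0.4 and a PPS improvement. The split would then be exploratory, with its definition and pooling rule left to an SAP that is not shown. Much of this stands. Section 11.2 does not call the split primary, and the all-patient reading is the more plausible one. A definition and a rule could indeed be given in an SAP. What the reply does not remove is the conflict inside the protocol, where the joint analysis is conditional in one section and required in another. An SAP would inherit it.

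A reader might also infer four stronger points that the protocol does not support:

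- **That the population is chosen after the results are seen.** Section 11.2 gives no timing, and sections 4 and 8 blind the statisticians of the main analysis. Blinding supplies no pooling rule, so a data-driven choice is a risk, not a fact.
- **That the split breaches intention to treat.** The two groups together contain every enrolled patient, so that sentence is met either way.
- **That the trial has a 10% to 11% chance of a false positive conclusion.** Those rates are for any two-sided MDI p-value below 5%, including apparent harm. Section 12 makes false success much rarer (Step 3).
- **That leaving the groups out of the minimisation biases the comparisons.** It does not bias either comparison in expectation; it only leaves balance within the groups uncontrolled.

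**Conclusion.** The point holds as a conflict between section 11.2 and sections 11.1 and 12 over which analysis carries the MDI conclusion. If both parts are tested, the two-sided error rate for MDI roughly doubles, from 5% to 9.8%, and lies between 8% and 11.5% depending on how the joint test enters. False claims of benefit rise from 2.5% to about 5% to 6%. The error rate of the full success rule is lower and depends on whether the 0.4 threshold is applied to all patients or to each part, which the conflict leaves open. The loss of power is material under any split examined, but its size rests on assumed group sizes and on 150 analysed patients per arm without loss. The sample size calculation itself reproduces and is not at fault.

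**What to change.** In section 11.2, state that the single primary analysis of MDI is the comparison of active with control in all randomised patients, at 5%, and remove the sentence that makes the joint analysis conditional. This aligns 11.2 with 11.1 and 12 and keeps the error rate at 5% and the joint power at 93% under the inputs above.

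If the sponsor wants the exhausted-options comparison, move it to section 11.5 as a secondary subgroup analysis. Define the group from data recorded at baseline, and assess it with a treatment-by-group interaction test. Keeping both parts as primary would cost more: with Bonferroni at 2.5% each, power at effect size 0.4 (normal approximation) is 58% in each half of an even split, or 24% and 80% for a 20/80 split.

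The cost is two or three sentences in the protocol, with no added patients or data beyond a baseline definition of the group. The change should be made and dated before allocation is unblinded.

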#### *6.3.4 Health economics (cost / benefit) analysis*

Data from the last 12 months prior to the inclusion date will be used as baseline variables. This is only executed if the primary and secondary effect objectives meet the criteria for success (see paragraph 12). Data will be collected for the following services:

1. Number of visits to the practitioner (for heart problems)
2. Number of visits to a cardiologist (specialist)
3. Number of hospital visits (outpatient)
4. Number of inpatient days in a hospital

5. Use of invasive procedures (PCI and/or CABG)
6. Use of cardiovascular medicine
7. Number of sick days due to heart disease (if the person is working)

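### Step 2 of the closed test procedure is a set of seven health economic items with no rule for deciding it, so 5% error control is not guaranteed at that step or for opening step 3

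*Protocol*

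**What the plan says.** Protocol section 11.2 sets one level throughout: "Five percent (5 %) will be used as significance level in all statistic tests". It then orders three hypotheses under a closed test procedure.

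- Step 1 is a single score: "The Ull Care program improves the degree of depression measured by a MDI depression score, measured after 3 months of intervention".
- Step 2 is plural: "Second priority hypothesis: The Ull Care program improves health economic variables, measured after 12 months of intervention".
- Step 3 is one outcome, defined as a composite in section 6.3.5: "Third priority hypothesis: The Ull Care program improves the frequency of clinical events, measured after 12 months of intervention".

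Section 6.3.4 introduces the health economic list with "Data will be collected for the following services" and gives seven items: visits to the practitioner, cardiologist visits, outpatient hospital visits, inpatient days, invasive procedures, cardiovascular medicine, and sick days (working patients only). The list stands among the tertiary variables, and section 11.2 has all tertiary variables analysed by variance and regression methods.

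Section 11.3 plans a cost-utility comparison of the arms at 12 months, with and without indirect costs, but does not call it the test of step 2. Sections 6.3.4 and 7 make the 12-month work conditional on meeting the success criteria of section 12.

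**The concern.** A fixed order of hypotheses protects the overall error rate only if each step is decided by one valid test at the stated level, and a later step opens only when the earlier one has been rejected. Step 2 has seven candidate variables plus an economic summary, and nothing says which of them decides it, or whether any one or all must be significant. The rule could therefore be chosen after the data are seen.

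Two things are at stake: a claim that the programme improves health economics, and the opening of step 3. The two are also related. The clinical event composite counts hospital visits and admissions for cardiac reasons, which overlap with the outpatient visits and inpatient days in section 6.3.4. A chance difference in hospital use could feed both claims. Lower use of health services and a better prognosis are stated 12-month aims in section 3, so these claims matter to the sponsor.

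**Working it through.** **Inputs.** Level per test: 5% (section 11.2). Number of items: k = 7 (section 6.3.4). Within-step adjustment: none stated. Planned power for step 1: 80% (section 11.1). Assumptions, because the protocol gives neither: tests are two-sided, and the seven test statistics share a common correlation ρ, varied from 0 to 1.

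**The plan's own figure.** The only error figure stated for step 2 is 5% per test. With one test, 1 − (1 − 0.05)¹ = 0.05, so the figure holds if step 2 is a single test.

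**If any one of seven is enough.** Suppose step 1 has been passed and all seven economic nulls are true.

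- Independent, two-sided: 1 − 0.95⁷ = 0.302.
- Upper bound under any correlation: 7 × 0.05 = 0.35.
- Independent, favourable direction only: 1 − 0.975⁷ = 0.162, against 0.025 for one test.

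Simulation of seven equally correlated normal statistics (400,000 draws) gives:

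| ρ | Any of 7, two-sided | Any of 7, favourable only |
|---|---|---|
| 0 | 0.302 | 0.163 |
| 0.3 | 0.271 | 0.137 |
| 0.5 | 0.230 | 0.115 |
| 0.7 | 0.178 | 0.089 |
| 0.9 | 0.114 | 0.057 |
| 1 | 0.050 | 0.025 |

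At ρ = 0.5 both columns are about 4.6 times the single-test rate (0.230/0.05 and 0.115/0.025).

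**Allowing for step 1.**

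- If the programme has no true effect on depression, any later false claim first needs a false rejection at step 1. The whole sequence stays at or below 5%.
- If the effect is real and step 1 is passed with the planned 80% chance, independently of the economic results, the two-sided figures become 0.8 × 0.302 = 0.24 and 0.8 × 0.230 = 0.18. The further criteria in section 12 would lower them again.

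**If another rule applies.**

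- One summary measure: 5%.
- All seven required: at most 5%.
- Bonferroni within the set: 0.05/7 = 0.00714 each, giving 1 − (1 − 0.00714)⁷ = 0.049 under independence and at most 5% under any correlation.

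So the error rate at step 2 runs from 5% or less to about 30% depending on a rule that the protocol does not state.

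**The case against.** A reader might infer that the protocol lets one significant item out of seven carry step 2, and hence that error control has failed. No sentence says so. The heading of section 6.3.4 and its wording about data collection allow the seven items to be read as inputs to one economic comparison, and section 11.3 plans such a comparison at the same time point. Analysing every tertiary variable does not make each one sufficient for the hypothesis. This stands: loss of control is one reading, not a stated fact.

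A reader might also infer that there is no protection from step 2 onward. That goes too far. The sequence holds at 5% if depression is not truly improved, and section 12 adds further conditions before any 12-month analysis. If step 3 is one valid 5% test, its own false-positive rate remains at most 5% even when it is opened by chance.

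The hypothesis says that the programme improves matters, so the favourable-direction figures describe a false claim better than the two-sided ones. The seven items are probably correlated, which puts 30% near the top of the range.

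Finally, the statistical analysis plan is not at hand and might name the rule. But the protocol has not left multiplicity open: it fixes the procedure, the order and the level for every test, and what it fixes at step 2 is not a single test. An all-seven rule would control the error, but it is not stated and fits poorly with an item that applies only to working patients.

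**Conclusion.** The point holds as a gap in the decision rule. Step 2 covers seven listed items at a flat 5% with no deciding variable, composite or adjustment, so the procedure guarantees 5% neither for a step 2 claim nor for the opening of step 3.

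The size depends on the missing rule. If any one item suffices, depression is truly improved, step 1 is passed and all seven economic nulls hold, the chance of a false step 2 result is about 30% under independence and 23% at an assumed correlation of 0.5 (two-sided, bound 35%). In the favourable direction it is about 16% and 11.5%, against 2.5% for one test. With a single summary or an all-seven rule it is at most 5%.

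The primary depression result and the success criteria are untouched. The change is worth making because the 12-month claims are stated aims and the remedy is cheap.

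**What to change.** In section 11.2, make step 2 one pre-named test. One workable choice is total direct health-service cost per patient, built from items 1 to 6 of section 6.3.4, over the 12 months after inclusion, compared between arms and adjusted for the same cost in the prior 12 months. State that sick days and indirect costs are excluded from this variable. Section 11.3 would otherwise leave that choice open, and sick days are not a health service. The prior-year adjustment uses the baseline that section 6.3.4 already plans. Step 3 opens only if this test is significant at 5%. The individual service items, sick days and the cost-utility result are then reported descriptively with confidence intervals.

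If claims on individual services are wanted, use Holm or Bonferroni (0.05/7) within the set and say when step 3 opens. It may be tested at the full 5% only if all seven are rejected. Under Bonferroni, a partial result passes on only its share, so m rejections allow step 3 to be tested at m × 0.05/7.

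The cost is a few sentences and no new data, since resource use is already to be collected for the cost-utility analysis. The downside is that the sponsor gives up unadjusted confirmatory claims on individual services.

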### **11.3. Cost-Utility analysis (CUA)**

A cost-utility analysis will be carried through after 12 months of intervention for comparison of active versus control treatment. Relevant data, meaning consumption of healthcare services such as hospital visits, ambulatory visits, use of medication, consumption of invasive procedures etc. will be gathered during the study. Data from SF-36 questionnaires will be used to generate OALY's based on the fact that the Minimal Important Difference (MID) in effect on physical health (PCS scale) and mental health (MCS scale) is 0,3 (calculated as shown in point 11.1) (Ware JE et al 2007). Estimations of indirect costs, such as social pensions will be included. CUA will be calculated both with and without the indirect costs.

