## 7.1 Flowchart:

| Visit (number)                             | 1      | 2          | 3         | 4                                  |
|--------------------------------------------|--------|------------|-----------|------------------------------------|
| Physical location                          | Herlev | Home visit | Herlev    | Data collection via public records |
| Months                                     | 0      | 0          | 3         | 12                                 |
| Window for visits                          |        | +/-7 days  | +/-7 days |                                    |
| Informed consent                           | X      |            |           |                                    |
| Questionnaires completed                   | X      |            | X         |                                    |
| Inclusion/exclusion                        | X      |            |           |                                    |
| Blood pressure, pulse, PPS and HRV test    | X      |            | X         |                                    |
| Blood sample                               | X      |            | X         |                                    |
| Assessment of medication                   | X      |            | X         |                                    |
| Randomization                              | X      |            |           |                                    |
| Registration of clinical events            | X      |            |           | X                                  |
| Consumption of healthcare services         | X      |            |           | X                                  |
| Implementation of joint treatment          | X      |            |           |                                    |
| Implementation of active treatment         |        | X          |           |                                    |
| Measurement of body composition (subgroup) | X      |            | X         |                                    |

CONSORT Flow Chart for the SongHeart study

[figure not shown]

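### The 12-month cost-utility analysis has SF-36 data only at months 0 and 3, and its QALYs are tied to a minimal important difference that is not a utility weight

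*Protocol*

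**What the plan says.** Section 11.3 sets the horizon: "A cost-utility analysis will be carried through after 12 months of intervention for comparison of active versus control treatment". Its source of QALYs (printed with an O) is the SF-36: "Data from SF-36 questionnaires will be used to generate OALY's based on the fact that the Minimal Important Difference (MID) in effect on physical health". That sentence gives one value for the physical (PCS) and mental (MCS) summary scales alike and closes with "mental health (MCS scale) is 0,3 (calculated as shown in point 11.1". Section 11.1 defines the quantity referred to: "Effect size is a fraction that consists of the difference in a MDI score from before intervention till after treatment for the active group". The corresponding change in controls is subtracted, and the result is divided by the SD of the change.

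On data collection, the flowchart in 7.1 has a row "Questionnaires completed" marked at visit 1 (month 0) and visit 3 (month 3) and blank at visit 4 (month 12). Visit 4 is described as "Data collection via public records" and is marked only for clinical events and healthcare consumption. The text of section 7 agrees: patients return at three months for a repeat of the baseline visit, and the 12-month analyses listed are service use and clinical events. Section 6.3.4, which lists the health-economic data, contains service-use and sick-leave items and no utility measure.

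**The concern.** A 12-month QALY needs a utility value over the whole year. Here the last questionnaire is at month 3, and the protocol does not say how months 3 to 12 are to be filled. The cost side would cover 12 months of records, while the quality-of-life side would rest on three months of data and an unstated extrapolation.

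The sentence that explains how QALYs arise also points to the wrong quantity. A minimal important difference is a threshold for judging a group contrast. It assigns no patient a value on a utility scale.

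At stake is the cost per QALY, which under section 6.3.4 would be produced only if the trial has met its success criteria. That is when readers would be most likely to rely on it.

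**Working it through.** The protocol states no QALY figure, so there is none to reproduce. The check has three parts.

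**1. Coverage of the horizon.**
- Horizon: 12 months (11.3).
- SF-36 measured at months 0 and 3 (7.1; section 7).
- Months without a utility measurement: 12 − 3 = 9; share 9/12 = 75%.

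The flowchart and the prose agree, so the blank cell at month 12 is not a table-reading error.

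**2. What the 0.3 is.** Section 11.1 gives effect size = (change in active − change in control) / SD of change. Its own example is (13 − 10)/7.5 = 3/7.5 = 0.4. The 0.3 for PCS and MCS is calculated in the same way. It is therefore unitless, belongs to a group contrast and carries no duration. A QALY is utility multiplied by time, summed for each patient. The 0.3 supplies neither term.

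**3. How much the unmeasured months matter.** Let the between-group utility difference be 0 at baseline and rise linearly to g at month 3. The QALY gain is the area under this difference, with time in years.
- Months 0–3: ½ × 0.25 × g = 0.125g.
- Months 3–12, full persistence: 0.75 × g = 0.75g.
- Months 3–12, linear fade to zero at month 12: ½ × 0.75 × g = 0.375g.
- Months 3–12, gain lost at once after month 3: 0.

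| Path after month 3 | 12-month QALY gain |
|---|---|
| Immediate loss (extreme case) | 0.125g |
| Linear fade to month 12 | 0.125g + 0.375g = 0.5g |
| Full persistence | 0.125g + 0.75g = 0.875g |

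Ratios: 0.875/0.5 = 1.75 between fade and persistence; 0.875/0.125 = 7 if the extreme case is included.

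The protocol gives no value for g. With assumed values, the three gains (immediate loss, fade, persistence) are:
- g = 0.02: 0.0025, 0.0100 and 0.0175 QALYs;
- g = 0.05: 0.00625, 0.025 and 0.04375 QALYs.

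For a fixed cost difference, the cost per QALY moves by the same factors in the opposite direction.

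**The case against.** Much can be said for the plan, and several stronger readings that a reader might infer do not hold.

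- **That no QALYs can be obtained.** Section 11.3 names SF-36 data as the source. The MID sits in an awkward subordinate clause and may be a misplaced relevance threshold, like those given for MDI and WHO-5 in 11.1. SF-36 items can be converted to utilities. What stands is that the stated basis does not do this.
- **That nothing is observed after month 3.** Service use and clinical events, including cardiac death (6.3.5), are followed to month 12. Only health-related utility is missing.
- **That the result is uncertain sevenfold.** That figure needs the whole gain to vanish at month 3. Patients keep a taught self-care technique and receive a personal meter, so some persistence is plausible. Between fade and persistence the factor is 1.75. The three paths are illustrations and not strict bounds.
- **That the analysis should be cut to three months of costs and effects.** This would match the measured utilities, but it would drop the planned comparison of 12-month service use, which is a stated aim in section 3. The flowchart marks service use only at visits 1 and 4.
- **That omitting the scoring index is itself an error.** The index and the area-under-the-curve details are commonly left to an analysis plan, which may exist. That answers the omission. It does not answer the MID wording, which is a misstatement in the protocol, and no analysis plan can supply questionnaires that were never scheduled.

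The importance is also limited. Section 6.3.4 makes health economics a tertiary item, run only on success, although 11.3 states the analysis without that condition. QALYs do not appear in the success criteria (section 12). Section 11.2 ranks health-economic variables second in its testing order but does not mention QALYs.

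**Conclusion.** The point holds in two limited parts. First, utility is unmeasured for 9 of the 12 months of the planned horizon, so a 12-month QALY gain depends on an assumption that the protocol does not state: 0.5g with linear fade, 0.875g with full persistence, and 0.125g in the extreme case of immediate loss. These figures assume equal utility at baseline and a linear rise to g at month 3. Second, the clause that bases QALYs on an MID of 0.3 is wrong as written, because that number is a standardised group difference and not a preference weight.

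A related inconsistency bears on persistence: 11.2 and 11.3 speak of 12 months of intervention, while section 7 gives an intervention period of 3 months. The primary MDI analysis is not touched. The change should be made, but the validity of the trial does not depend on it.

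**What to change.** 1. In 11.3, delete the MID as the basis for QALYs and state that the SF-36 items will be scored with a preference-based index such as SF-6D. Cost: amendment wording and standard scoring.
2. To keep the 12-month horizon, mail the SF-36 to both groups at month 12 and add it to the flowchart. Cost: one more questionnaire, with some non-response to handle.
3. If no month-12 questionnaire is added, label the 12-month cost per QALY a scenario analysis and state the persistence and fade assumptions in advance. Cost: none in data, but the result is then openly assumption-driven.
4. Reconcile the 12 months of intervention in 11.2 and 11.3 with the 3-month period in section 7, and align 11.3 with the success condition in 6.3.4. Cost: wording only.
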